### **6.6.3 Self-monitoring ketones**

For safety purposes, participants will be required to self-monitor either urine or blood ketones regularly throughout the intervention period using their usual method(s) of measuring ketones. Participants will be required to measure their ketones at least twice per week, and more under certain circumstances (e.g., if feeling unwell) as per standard of care diabetes practices. To assist participants in doing this, the required amount of ketone test strips will be provided. A resource titled, 'Self-monitoring ketones' (Attachment 52) will be provided at the beginning of the intervention period to instruct participants on how and when to monitor for ketones, what level of ketones are and are not expected, and what to do if they are experiencing unexpected changes in blood or urine ketones. The resource will help participants understand that mild, controlled ketone readings are normal and expected with the LC dietary intervention. Nutritional ketosis is typically defined as a ketone reading within the range of 0.5–3.0 mmol/L [23] and should not be confused with DKA that is associated with a rapid increase in ketone levels typically 10 times the level observed with nutritional ketosis. Nevertheless, we are taking a conservative approach and advising participants to maintain ketones  $\leq 0.6$  mmol/L, as per usual standard diabetes practice. The resource, 'Self-monitoring ketones' (Attachment 52), includes guidelines on when to monitor for ketones, and what action to take if ketones are  $>0.6$  mmol/L. In brief, participants will be advised to refer to the resource titled 'Managing sick days' (Attachment 43) for more information. In any case, participants will be instructed to immediately inform [name] (study dietitian) of any instances where ketones are  $>0.6$  mmol/L and the case will be flagged with the study endocrinologist. The overseeing endocrinologist will then make a decision to either (a) continue as is or under certain condition (e.g., need to monitor

ketones once daily); (b) refer them to their nominated HCP or GP for independent review; or (c) refer them to the study diabetes educator or study physician for review. If [name] is unavailable, then [name] will be consulted to review the case. All cases referred will be documented and used to assess safety of the intervention in the data analysis and reporting.

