| OBJECTIVES              | The aim of this research is to assess the efficacy of a low-carbohydrate (LC) diet in adults with type 1 diabetes (T1D). We will specifically set out to determine whether significant differences in T1D management outcomes exist between a LC diet and habitual diets higher in carbohydrate.                                                                                                                                                                                                                                                                                                                                                                                                  |
| PRIMARY HYPOTHESIS      | A low-carbohydrate (LC) diet will result in improved type 1 diabetes management compared to habitual diets higher in carbohydrates.                                                                                                                                                                                                                                                                                                                                                                                                                                                                                                                                                               |
| DESIGN                  | This is a 28-week single arm within-participant intervention study involving a 4-week control period, a 12-week intervention period and a 12-week follow-up.                                                                                                                                                                                                                                                                                                                                                                                                                                                                                                                                      |

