## 10. DATA MANAGEMENT

### 10.1 Data collection

We will be collecting data from the following sources:

- Online survey (including consent form)
- Email correspondence (participants may email data to [name])
- Clinical documents provided by participants and/or their HCPs
- Pathology results provided by iMedical
- Outcome measurements taken at study visits with the study dietitian (e.g., weight, waist circumference, blood pressure, questionnaires)
- Self-monitoring data provided by participants (e.g., glucose logs, insulin dosing logs, dietary intake data)

- Any other relevant information provided by participants at any time-point throughout the study (e.g., details of adverse events, change(s) to other medications, etc.)

All data collected about participants for this study will be promptly recorded or uploaded directly onto the University's preferred platform of REDCap. REDCap is a secure, password-protected online database platform, with access to this project limited to the individuals named on this ethics application. REDCap allows participants to upload relevant documentation that may be required during the online screening survey (e.g., evidence of T1D diagnosis). If participants do not have the relevant documentation available at the time of completing the survey, they may email it to [name] or provide it in-person once obtained. In these cases, [name] will be responsible for uploading the data collected via email (electronic document/s) or in-person (hard document/s) onto REDCap as soon as possible, before destroying the original electronic document/s (from her email inbox and/or downloads folder) or returning the hard document/s to participants. Data collected by the study dietitian or study physician at any time-point throughout the study will be recorded directly into specific data collection templates hosted on REDCap.

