| Diet session 2
(during week 7)  | 
 
• Telehealth call (Zoom) with study dietitian.
 
• Review of dietary intake (collect diet history or review Easy Diet Diary tracking) and usual care blood glucose monitoring.
 
• Provide individualised dietary strategies for adhering to the intervention.
 
• Review understanding of information provided in diet session 1.
 
• Diet resources discussed in this session:               
 
- Dietary proteins
 
- Dietary fats
 
- Snack ideas
 
 
 
• Participants prompted to report any adverse events experienced (self-report) over previous 2 weeks (e.g., hypoglycaemia (<3.5 mmol/L), digestive issues, low energy levels, headaches, etc.)
 
• Participants encouraged to follow-up with their nominated healthcare professional to discuss insulin management.
 
                                                                                                                                                                                                                                                                                                                                          |

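### The protocol specifies no collection of ketone readings or of tests done, so a low count of raised-ketone cases cannot be told apart from under-testing or under-reporting

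*Protocol*

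**What the plan says.** Section 6.6.3, repeated in Section 7.3.4, has participants test "either urine or blood ketones regularly throughout the intervention period using their usual method(s) of measuring ketones". The minimum frequency is fixed: "Participants will be required to measure their ketones at least twice per week, and more under certain circumstances". Strips are supplied.

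If a reading is above 0.6 mmol/L, "participants will be instructed to immediately inform" the study dietitian, who flags the case to the endocrinologist. The endocrinologist may let the participant carry on (with or without conditions), refer to the nominated practitioner or GP, or refer to the study diabetes educator or physician. The section closes: "All cases referred will be documented and used to assess safety of the intervention in the data analysis and reporting".

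In Table 1 (Section 15), the review item at diet sessions 2 to 6 reads "Review of dietary intake (collect diet history or review Easy Diet Diary tracking) and usual care blood glucose monitoring". Ketones appear in Table 1 only as an education resource, at diet session 1 and at the diabetes education session. Section 10.1 lists "Self-monitoring data provided by participants (e.g., glucose logs, insulin dosing logs, dietary intake data" among its sources, and closes with an open item: "Any other relevant information provided by participants at any time-point throughout the study". Ketones are not among the outcomes in Section 9.

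**The concern.** The protocol commits to using ketone cases as safety evidence but specifies only how a numerator arises. That numerator depends on three things: how often ketones are raised, how many tests are done, and how many raised readings are reported. Only their product would be seen. A participant who stops testing leaves the same record as one who tests faithfully and stays below the limit, and the dietitian has no scheduled means of telling them apart.

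Other safety items are actively sought. Glucose data are requested every fortnight (Section 7.3.2), medication changes are asked about at each diet session (6.6.4), and symptoms of sodium deficiency are checked at each session (7.3.3). Ketones are not, although they are monitored because of DKA, which Section 7.3.4 treats as an emergency.

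Under-reporting is foreseeable from the text itself. Participants are told that mild readings are expected, with nutritional ketosis put at 0.5 to 3.0 mmol/L, while the reporting trigger of 0.6 lies inside that range. This is no comment on where the limit should be; it shows only that unprompted reporting is fragile here.

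The numerator may also be incomplete. Only referred cases are said to be documented, so a flagged case that the endocrinologist allows to carry on may not be counted.

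**Working it through.** The protocol gives no ketone count or rate to reproduce. The check is what a count could mean under the plan as written.

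**Inputs from the protocol**
- Minimum frequency: 2 tests per week (Section 6.6.3).
- Duration: the intervention part of "a 4-week control period, a 12-week intervention period and a 12-week follow-up" (Section 2), so 12 weeks.
- Participants: 20 recruited; with 20% dropout (Section 6.2), 20 × (1 − 0.20) = 16 completers.

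**Required minimum**
- Per participant: 2 × 12 = 24 tests.
- 20 participants: 20 × 24 = 480.
- 16 completers: 16 × 24 = 384.

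The number done is not captured, and extra tests, for example when unwell, have no fixed ceiling.

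**Same count, different ketosis.** Expected reports = required tests × share done × share of readings above the limit × share reported. The shares are assumptions, with reporting set at 100%:
- all tests done, 5% raised: 480 × 1.00 × 0.05 = 24
- half done, 10% raised: 480 × 0.50 × 0.10 = 24
- a quarter done, 20% raised: 480 × 0.25 × 0.20 = 24

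A fourfold range in true frequency gives the same count. Incomplete reporting would widen it.

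**Five reported readings (assumed), by tests actually done.** Rate = 5/T, with the exact (Clopper-Pearson) 95% interval:

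| Tests done, T | Rate | 95% CI |
|---|---|---|
| 480 | 1.0% | 0.3 to 2.4% |
| 240 | 2.1% | 0.7 to 4.8% |
| 120 | 4.2% | 1.4 to 9.5% |
| 48 | 10.4% | 3.5 to 22.7% |

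**No reported readings.** The one-sided 95% upper bound per test is 1 − 0.05^(1/T): 0.6% for T = 480 and 6.1% for T = 48.

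These intervals treat tests as independent and all raised readings as reported. Readings within a participant are likely to be correlated, so the real uncertainty would be wider.

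**The case against.** A reader might infer that ketone values are never collected and that participants may choose which ones to declare. The protocol does not support that. Reporting above 0.6 mmol/L is an instruction. The source list in Section 10.1 and the adverse-event prompts in Table 1 are open-ended. Attachment 52, which governs ketone monitoring, is not shown, so a log there cannot be excluded. What can be said is that the text shown specifies no such collection.

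A reader might also infer that DKA itself could be missed, or that non-testers will be scored as safe. DKA is a listed adverse event in Section 8.1, with its own reporting and documentation route (8.1, 8.2), and no passage classes anyone as event-free. A raised reading alone is different: Section 8.1 requires that health care was needed and that the event was attributed to the study, so such a reading need not enter by that route.

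It is fair to add that ketone testing is an alert for the individual rather than a study outcome, and that participant and person-time denominators exist. Neither corrects for under-testing. How safety counts are presented may properly wait for the analysis plan, but that plan cannot restore readings or test counts that nobody recorded.

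Finally, a plain share of tests above the limit would be biased, because Section 6.6.3 calls for extra tests when unwell and daily testing may be ordered after a high reading. That stands, and the fix allows for it.

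**Conclusion.** The point holds as a gap in data collection. As written, the raised-ketone result has no per-test denominator, and a low count cannot be separated from under-testing or under-reporting. The required minimum of 480 tests (384 for completers) follows from the protocol. The spread from 1.0% to 10.4% for five reports rests on assumed counts and assumed testing levels; it shows how far the reading of one count can move and is not an estimate of what will happen. The primary outcome and the capture of overt DKA are unaffected. The conclusion would soften if Attachment 52 contains a log that is collected; the protocol should then cite it and schedule its return. This is a cheap, worthwhile improvement and not a fatal flaw.

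**What to change.** - **Record.** At diet sessions 2 to 6 and clinic visit 6, alongside the existing glucose review where there is one, enter every ketone reading in REDCap: date, value, blood or urine, and whether it was scheduled or triggered by illness or by a prior high reading.
- **Name it.** Add ketone readings to the self-monitoring data in Section 10.1 and to the review items in Table 1.
- **Document all flagged cases**, whatever the endocrinologist decides, and not only those referred.
- **Report** tests done against the required minimum, the number of participants with at least one raised reading, and the share of scheduled tests above the limit, kept separate from triggered tests and split by blood or urine.
- **Describe** participants without readings as not assessed.

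The limit and the clinical actions stay as they are. The cost is one set of REDCap fields and a few minutes of data entry per session; strips are already supplied. The readings remain self-reported, so under-reporting is reduced but not removed, and the safety statement may become less favourable.

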device, as per standard of care diabetes practice. They will also be encouraged to test their blood glucose levels before going to bed and before driving or participating in exercise. Participants will also be advised to test their glucose more often if they are: feeling sick or stressed; more or less physically active; experiencing more hypos than usual; experiencing changes in their routine; experiencing night sweats or morning headaches; noticing frequent instances of high blood glucose levels; and/or starting on new medications. Participants will be asked to provide their blood glucose data from their blood glucose monitoring device to the dietitian for review every fortnight throughout the study. If using a CGM or flash glucose monitor (FGM), any reading(s)  $<4$  mmol/L should be confirmed with a finger prick device. If two or more readings across a 14-day period are  $<4.0$  mmol/L then the dietitian will flag the case with the study endocrinologist. The overseeing endocrinologist will then make a decision to either (a) continue until the next review (14 days); (b) refer them to their nominated HCP or GP for independent review; or (c) refer them to the study diabetes educator or study physician for review. If [name] is unavailable, then [name] will be consulted to review the case. All cases referred will be documented and used to assess safety of the intervention in the data analysis and reporting. Participants with hypo unawareness will be excluded from participating in the study. However, if any participant believes they might have developed hypo unawareness during the study, they will be advised to contact [name] (study dietitian) as soon as possible, who will flag the case with the study endocrinologist to be assessed on an individual basis.

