### **7.3.5 Psychological or emotional stress**

Any change(s) in chronic disease management, including an increased awareness of disease state (e.g., increased frequency of blood glucose monitoring), can be psychologically demanding and/or emotionally distressing. Health assessments included as part of the study may also bring up underlying psychological/emotional issues (e.g., emotional relationships with food). At the onset of the study (start of control period, Table 1), participants will be provided with an NDSS fact sheet relating to diabetes distress which includes contact details for free counselling/support services that participants can access at any time during or after the study (<https://www.ndss.com.au/wp-content/uploads/fact-sheets/fact-sheet-diabetes-distress.pdf>). Participants will also be provided opportunity to discuss any issues they may be experiencing with the study dietitian during regular diet consults. The dietitian will flag any psychological issues or emotional stress with the study physician or the participants' nominated HCP and/or GP who may then refer participants to the appropriate health professional service for management.

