### 9.2 Secondary outcomes

- Glycaemic variability (GV) markers (including Standard Deviation (SD) intraday and mean amplitude of glycaemic excursions (MAGE) [derived from 7-day CGM/FGM data]
- Frequency of hypoglycaemia (<3.5 mmol/L with or without symptoms) [derived from 7-day CGM/FGM data]
- Total daily insulin (TDI) [the sum of all long-acting and rapid-acting insulin given over a 24-hour period derived from a 3-day self-report insulin log]
- Quality of life [measured using the 15-item DQOL Brief Clinical Inventory [25]]

GV markers have been identified as independent risk factors for diabetes complications including CVD, underscoring the importance of this assessment to more rigorously evaluate the effect(s) of the diet intervention on diabetes management.

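### On its wording, the ketone safety assessment counts only referred cases, so a reported reading above 0.6 mmol/L that the endocrinologist lets continue need not be counted

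*Protocol*

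**What the plan says.** Protocol section 6.6.3 (Self-monitoring ketones), repeated in section 7.3.4 (Diabetic ketoacidosis), sets up four steps.

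1. During the intervention period participants test urine or blood ketones at least twice a week, and more often in circumstances such as illness.
2. They tell the study dietitian at once of any reading above 0.6 mmol/L, and "the case will be flagged with the study endocrinologist".
3. "The overseeing endocrinologist will then make a decision to either (a) continue as is or under certain condition", or (b) to refer the participant to their own practitioner or GP, or (c) to refer them to the trial's diabetes educator or physician.
4. "All cases referred will be documented and used to assess safety of the intervention in the data analysis and reporting".

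No criterion is given for choosing among (a), (b) and (c). Ketones are not among the primary, secondary or additional outcomes in sections 9.1 to 9.3.

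**The concern.** Step 2 covers every reported exceedance. Step 4 commits only *referred* cases to the safety assessment. Decision (a) lies between them and is not a referral. Read plainly, the protocol does not oblige anyone to count an exceedance that the endocrinologist lets continue.

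This matters because the diet is expected to raise ketones, the trial has one open arm, and the decision is made by a clinician on the study team. A count of referrals describes how that clinician used discretion. A reader of the final report could take few referred cases to mean few exceedances, and the text as it stands does not rule out that misreading.

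**Working it through.** The protocol gives no figure for this point, so there is nothing to reproduce. The check compares the text of several sections, with a little arithmetic for scale.

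**Which decisions are counted.** Let E be the number of reported readings above 0.6 mmol/L, and let a, b and c be the numbers settled by each decision. Then:

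- E = a + b + c (all flagged cases);
- committed to the safety assessment on the plain wording = b + c;
- not committed = E − (b + c) = a.

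Two of the three permitted decisions are counted and one is not. These are options, not cases. Since no criterion for choosing is stated, the size of a cannot be derived.

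**Whether (a) could be a common decision.** Section 6.6.3 says that mild, controlled readings are to be expected on this diet, and gives nutritional ketosis as 0.5 to 3.0 mmol/L. The part of that range above the limit is (3.0 − 0.6) / (3.0 − 0.5) = 2.4 / 2.5 = 96% of its width. This is a share of the range, not of readings, and participants are advised to stay at or below 0.6 mmol/L. It shows only that a reading can exceed the limit and still be one the protocol calls expected, for which (a) would be a natural choice.

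**Whether flagging and referring are the same act.** In sections 6.6.3 and 7.3.4 the step to the endocrinologist is called flagging, and the verb *refer* appears only in (b) and (c). Section 7.3.5 has the same sequence. Its first step is: "The dietitian will flag any psychological issues or emotional stress with the study physician". Referral is a separate, later step that is permitted but not required, and it falls to whichever clinician was told; where that is someone from usual care, the text reads: "nominated HCP and/or GP who may then refer participants to the appropriate health professional service for management". Flagging comes first, and referral may follow.

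**Whether another stated rule counts the (a) cases.**

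| Place in the protocol | What it captures | Does it commit (a) cases to a count? |
|---|---|---|
| 8.1 Adverse event definitions | Incidents that need health care and are attributed to the study; ketoacidosis is listed by name | No, unless health care was needed |
| 9.1 to 9.3 Outcomes | No ketone measure | No |
| 10.1 Data collection | "All data collected about participants for this study will be promptly recorded or uploaded directly onto" REDCap | Storage is likely; counting is not required |
| Table 1, diet sessions 2–6 | Adverse events or side effects, with open example lists that do not name ketones | Not stated |

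**Comparison with hypoglycaemia.** Section 7.3.2 has the same pattern. If two or more readings in 14 days are below 4.0 mmol/L, "then the dietitian will flag the case with the study endocrinologist", and the same sentence about referred cases follows. But section 9.2 also lists "Frequency of hypoglycaemia (<3.5 mmol/L with or without symptoms) [derived from 7-day CGM/FGM data" as a secondary outcome, and that measure does not depend on any referral. Ketones have no such second measure.

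**Scale of monitoring.** The required minimum is 2 readings per week × 12 weeks = 24 per participant. That is 24 × 20 = 480 for the planned recruitment, or 24 × 16 = 384 for the sample-size target. Time at risk, if all complete the intervention, is 12 × 20 = 240 or 12 × 16 = 192 participant-weeks.

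**The case against.** The best reply is that *cases referred* may mean cases sent to the endocrinologist. In section 6.6.3 the noun *case* is used for the item the endocrinologist reviews, whereas (b) and (c) refer persons. The sentence also directly follows the one on who reviews the case if the endocrinologist is unavailable. This reading is possible. It goes against the flag-then-refer usage in the same paragraph and in section 7.3.5, but section 7.3.5 concerns psychological distress and does not settle the matter. If the sponsor meant all flagged cases, changing one word says so.

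It is also fair to say that the sentence is a commitment and not an exclusion. Nothing forbids counting (a) cases, and a later analysis plan could tabulate them from REDCap. That stands, and it keeps the point minor. It does not remove the point, because the protocol itself fixes what will be used to assess safety.

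Stronger inferences are tempting, and the protocol does not support them:

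- *Ketoacidosis could go unreported.* Section 8.1 names it as an adverse event, and section 8.2 has all adverse events documented regardless of the endocrinologist's decision.
- *No rate can be given without the number of readings taken.* The proportion of participants with at least one exceedance, and exceedances per participant-week, need no such number.
- *The twice-weekly readings are never collected.* No visible step names their return, whereas section 7.3.2 asks for glucose data every fortnight. But Attachment 52 and Figure 1 are not available here, and the list of self-monitoring data in section 10.1 is open.

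**Conclusion.** The point holds as a minor reporting defect. On the plain wording of sections 6.6.3 and 7.3.4, one of the three permitted outcomes of an endocrinologist review falls outside what must be counted, so the ketone safety count rests on discretion and not on how often 0.6 mmol/L was exceeded.

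The number of cases affected is unknown: it depends on how often (a) is chosen, and the protocol gives no basis for estimating that. The conclusion assumes that *referred* carries the meaning it has in (b) and (c).

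Every reported exceedance still reaches the endocrinologist, so immediate protection is intact. The HbA1c analysis is not touched.

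**What to change.** Keep the 0.6 mmol/L limit and the endocrinologist review.

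1. In sections 6.6.3 and 7.3.4, replace the phrase limiting the commitment to referred cases with: *All cases flagged (any reported reading above 0.6 mmol/L)*.
2. Report the number of participants with at least one exceedance and the number of exceedances per participant-week of intervention, each broken down by the endocrinologist's decision (a, b or c).
3. Optional and secondary: at diet sessions 2–6 and clinic visit 6, which already take place, ask for the ketone readings and the method (urine or blood). This would show adherence to twice-weekly testing and any exceedances that were not reported.

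Items 1 and 2 cost one phrase in two sections and a record of the decision taken. Item 3 adds a little data entry. The downside is a higher count that includes expected mild ketosis, which is why the decision should be shown beside it.
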